## 3 PRECLINICAL EXPERIENCE

### 3.1 Preclinical experience with rcAd26

The vaccine candidate proposed for this Phase 1 clinical study is a replication competent human adenovirus serotype 26 (rcAd26), used as a vaccine vector to deliver a MOS1.HIV-Env transgene. The vaccine is referred to as rcAd26.MOS1.HIV-Env and is an Ad26 virus with the E3 and part of the E4 genes (orf 1-4) deleted to allow the MOS1.HIV-Env transgene to be inserted. Adenoviruses are generally highly species specific and the human Ad26 virus is not known to replicate in any laboratory animal. However, the *in vitro* replicative fitness of rcAd26.MOS1.HIV-Env growth can be assessed in human cell lines. In addition, *in vivo* immunogenicity studies can be performed in mice and rhesus monkeys, with the understanding that the vector will be replication incompetent in these species. These assessments were performed at CVVR as part of the preclinical evaluation of rcAd26.MOS1.HIV-Env and are summarized below.

#### 3.1.1 *In vitro* characterization of rcAd26

The infectivity and growth kinetics of rcAd26 vectors were assessed in human cell lines to study how the deletion of E3/E4 and the insertion of the MOS1.HIV-Env transgene resulted in viral attenuation. Here, attenuation is defined by virus titer required to infect cells and the time to achieve maximum cytopathic effect (CPE). The cell lines used included A549 (epithelial lung carcinoma cells), HuTu 80 (duodenum adenocarcinoma cells), and Per55K (epithelial cells that complement the Ad E1 region). The rcAd26 vectors used in this study included the clinical candidate (rcAd26.MOS1.HIV-Env) and wild-type Ad26, as well as other versions of the vector that had either the E3 or E3/E4 region deleted, or were with or without the MOS1.HIV-Env transgene. Non-replicating versions of these vectors were also assessed.

The *in vitro* replicative capacity of all rcAd26 vectors was significantly reduced as compared to wild-type Ad26 in human epithelial and duodenal cells. Decreased *in vitro* replicative capacity occurred in a step-wise fashion with vectors containing only the E3 deletion having only a slight reduction, then becoming more reduced as both E3 and E4 were deleted. Replicative capacity was most reduced in vectors containing the HIV-1 Env transgene, with the clinical candidate rcAd26.MOS1.HIV-Env having the most pronounced decrease in replicative capacity, with approximately 100-fold more virus required to achieve the same virus growth compared to wild-type Ad26. As expected, the non-replicating Ad26 vectors did not replicate in either the A549 or HuTu 80 cell lines. As a control, the vector growth in E1-complementing PER.55K cells was evaluated. The data show that there was no significant difference in growth between the various Ad26 vectors as compared to wild-type when PER.55K cells were infected.

The *in vitro* infectivity of rcAd26 vectors was also compared to Ad4-H5-Vtn, an Ad4-based vector expressing influenza antigens which was recently found safe in a previous clinical trial. The rcAd26.MOS1.HIV-Env vaccine had a significantly decreased replication capacity compared to Ad4-H5-Vtn in A549 and HuTu 80 cells. In these cell lines, wild-type Ad26, wild-type Ad4 (Ad4.WT), and Ad4-H5-Vtn all grew equally well with rcAd26.MOS1.HIV-Env having significantly decreased growth in comparison. As expected, all vectors grew well in PER.55K cells. Finally, the ability of rcAd26 to infect

rhesus monkey cells (MK2, kidney cell line) was assessed. No CPE was seen at any MOI out to 6 days post-infection when rcAd26 vectors were used to infect MK2 cells.

In summary, the rcAd26.MOS1.HIV-Env vaccine had at least a 100-fold less replicative capacity compared with wild-type Ad26. In addition, growth of rcAd26.MOS1.HIV-Env was significantly reduced *in vitro* as compared to Ad4-H5-Vtn, a vector shown to be safe in a previous clinical trial. Finally, no evidence of rcAd26 virus replication in terms of CPE was detected in the rhesus monkey cell line MK2.

### 3.1.2 *In vivo* characterization of rcAd26

The immunogenicity of rcAd26.MOS1.HIV-Env was first assessed in Balb/c mice. Four mice were immunized by intramuscular (IM) injection with  $10^9$  vp of vaccine, sacrificed at 28 days, and the splenocytes assessed by IFN- $\gamma$  ELISPOT. Env-specific ELISPOT responses were detected in all mice. To assess if the immunogenicity of lyophilized rcAd26.MOS1.HIV-Env had been affected by lyophilization, Balb/c mice (n=4) were also immunized by IM injection with  $10^8$  or  $10^9$  vp of two different lots of reconstituted lyophilized rcAd26.MOS1.HIV-Env, as well as bulk drug substance. This study showed that lyophilized and reconstituted rcAd26.MOS1.HIV-Env remained infectious as well as immunogenic when compared to non-lyophilized rcAd26.MOS1.HIV-Env in terms of PFU, ELISPOT and ELISA assays. Finally, *in vivo* replication of replication-incompetent Ad26 was compared to that of replication-competent rcAd26 in mice by immunizing Balb/c mice (n=4) with  $10^{10}$  vp IM injection or intra-nasally (IN). The HIV-1 specific antibody responses were similar for the replication and non-replication product given either by IM or IN administration in these studies. The T-cell responses were much greater when the vectors were given by IM administration. There was no evidence of replication of vectors in mice. Though no safety data was collected in these non-GLP studies, all mice in all groups appeared healthy and well and no adverse effects in mood or physical appearance were observed.

Next, the immunogenicity of rcAd26 was assessed in nonhuman primates (NHP). Rhesus monkeys (Macaca Mulatta) (N=3/group) were immunized by IM injection with  $10^{11}$  vp with replicating E1(+) and non-replicating E1(-) Ad26-SIVGag vectors at weeks 0 and 24. IFN $\gamma$ -ELISPOT was performed at weeks 0, 2, 24, 26 and 32 to determine immune response. RT-PCR on serum was done at weeks -1, 1, 4, 6, 8, 10, 12 and 16 to look at virus replication. Both replication-competent and replication-incompetent Ad26.SIVGag were immunogenic in non-human primates. There was no evidence by RT-PCR that the replication-competent vector replicates in NHP.

In the non-GLP NHP immunogenicity study depicted above, various non-GLP safety assessments were made in the three NHPs that received the rcAd26-SIVGag vector at week 0 and week 24 by IM injection. Note that these studies were designed as small immunogenicity studies and were not specifically designed as safety studies. The safety observations were as follows: (1) No clinical adverse events (AEs) were observed in the three NHPs following immunization with  $10^{11}$  vp rcAd26-SIVGag. Non-GLP clinical observations included daily assessments of behavior, feeding patterns, and local and/or systemic reactogenicity as well as weekly assessments of body weights by senior veterinarians and veterinary technicians at New England Primate Research Center (NEPRC), Southborough, MA, which is affiliated with Harvard Medical School. (2) No clear changes in hematology parameters were observed in the three monkeys following immunization with  $10^{11}$  vp rcAd26-SIVGag, with the exception of mild decreases in

hematocrit as a result of the maximum allowable blood draws that were performed to facilitate the immunogenicity studies. Non-GLP blood hematology included assessments of white blood cell counts, hematocrit, cellular differentials, and T cell subpopulations. (3) No clear changes in serum chemistries were observed in the three monkeys following immunization with  $10^{11}$  vp rcAd26-SIVgag at week 0 and week 24. Non-GLP serum chemistries included assessments of electrolytes, renal function, hepatic function, and other chemistries.

### **3.1.3. Preclinical experience with non-replicating Ad26 vectors expressing Env**

Formal toxicology studies of rcAd26.MOS1.HIV-Env were not performed as the rcAd26 vector does not replicate in animals. The non-replicating Ad26 vector (E1 deleted), however, has been assessed in a GLP single-dose biodistribution study and a GLP repeated-dose toxicity study in New Zealand white rabbits performed at Avanza Laboratories (formerly Bridge Global Pharmaceutical Services / GeneLogic), Gaithersburg, MD. The biodistribution study (Bridge GPS Study No.1645-06074) demonstrated that IM administration of Ad26.ENVA.01 was well tolerated in male and female New Zealand white rabbits. Ad26.ENVA.01 remained primarily in the injection site muscle and distributed only to the iliac lymph nodes and spleen. Over the time course of the 91-day study, Ad26.ENVA.01 was shown to clear from inoculated animals as was indicated by the decline in percentage of animals with positive tissues (from a majority or all of the animals to only 1-2 animals) and the copy numbers detected (declining by more than 1-2 logs). The repeated-dose toxicity study also found that 4 repeat IM administrations of Ad26.ENVA.01 at doses up to  $10^{11}$  vp were well tolerated in male and female New Zealand white rabbits and did not result in any toxicologically significant effects. Changes in some clinical pathology, hematology and immunology parameters as well as histopathological findings at the injection site were consistent with an inflammatory response to the vaccine administration.

## **3.2 Preclinical experience with MOS1.HIV-Env**

The mosaic HIV-1 Env immunogen (MOS1.HIV-Env) has been evaluated extensively in mice and nonhuman primates. In addition to the studies described above, [name] et al. assessed cellular immune responses to mosaic HIV-1 vaccines in rhesus monkeys immunized with a single dose of non-replicating Ad26 expressing mosaic, consensus, or natural HIV-1 Gag, Pol, and Env sequences. The breadth and depth of T cell responses (measures of T cell epitope diversity) were greatest for the mosaic antigens compared to consensus and natural sequences. Mosaic Env immunogens also elicited non-inferior antibody responses as compared with the consensus or natural sequence Env antigens following heterologous boost. Similar results were seen in a mosaic vaccine study in NHP by Santra et al.. In a challenge study, rhesus monkeys were immunized with Ad26, Ad35, and MVA vectors expressing mosaic HIV-1 Env, Gag, and Pol in different prime/boost combinations, and were subsequently challenged with 6 low-dose, intrarectal challenges with SHIV-SF162P3. Both the Ad/MVA and Ad/Ad vaccines afforded partial protection against acquisition of SHIVSF162P3 infection, corresponding to an 87-90% reduction of per exposure acquisition risk, although the majority of the vaccinees became infected by the end of the challenge series. The vaccinees also exhibited a modest but significant 0.64 log reduction of setpoint viral loads, which was measured 84 days after infection, as compared with the controls.

Recently, an NHP challenge study addressed correlates of protection by interrogating virus sequences and vaccine-induced immune responses following immunization with mosaic immunogens. Animals were vaccinated with DNA and Ad5 expressing either mosaic Gag or mosaic heterologous Env, or heterologous Env based on a natural SIVmac239 sequence. The authors found that Env-elicited immune responses were necessary and sufficient to provide protection from acquisition from intrarectal SIVsmE660 with a strong sieving effect of Env immunization, selecting for minor variants in the challenge swarm. There was no association between protection from infection and protection from pathogenesis, suggesting that humoral responses that effectively block acquisition are not necessarily correlated with cellular responses that control pathogenesis. The Env-induced CTL also suppressed acute viremia better than Gag CTL resulting in reduced transmitted-founder viruses in breakthrough infections.

As noted above, formal toxicology studies of rcAd26.MOS1.HIV-Env were not performed as the rcAd26 vector does not replicate in animals. The MOS1.HIV-Env insert, however, has been assessed in a repeated dose GLP toxicity and local tolerance study of the Modified Vaccinia Ankara (MVA) vector expressing the same Mosaic Env sequence in New Zealand white rabbits. Vaccine-related changes in body temperatures, clinical pathology parameters, and pathology data were generally resolved and/or were trending toward recovery, were not deemed to be adverse, and were considered a normal immunologic/inflammatory response to the vaccine administration. None of these effects during the study for animals were adverse to the health of the animal.

acquired immunodeficiency syndrome (AIDS) . Surveillance sampling also recovered Ad26 from the stool of 2 patients with AIDS in England , and 2 HIV-1-infected patients in Lima, Peru . In addition, Ad26 was identified in the central nervous system (CNS) of a patient with medulloblastoma following irradiation and ventriculo-peritoneal shunt placement; this is the only report in the literature of Ad26 isolated outside the gut . Interestingly, Ad26 has not been identified among adenovirus isolates in the transplant population, including in 22 children following liver transplant , and in 19 children and 35 adults following bone marrow transplant .

## **4.2 Clinical experience with oral, live adenovirus vaccines**

The above data suggest that Ad26 infection produces subclinical enteric disease, and would be an appropriate vector to deliver vaccine antigens to the gut mucosa. In addition, oral, live attenuated adenovirus vaccines have a proven track record of safety and efficacy for the prevention of Ad4 and Ad7 respiratory illness . These vaccines have been administered safely to more than 10 million people over the span of nearly sixty years  to prevent mini-epidemics of debilitating and even life-threatening adenovirus disease in military recruits . Oral, live recombinant Ad4 (Ad4-H5-Vtn) has also recently been shown safe and immunogenic as a vector to express influenza antigens in humans . In addition, these oral adenovirus vaccine studies have provided data on vaccine shedding in stool among volunteers. In the clinical trial of Ad4-H5-Vtn, shedding was first detected, and detected in the most volunteers, at day 7 following immunization, and after day 14 was not detected in any volunteer . Similar patterns of shedding were also observed in studies of oral Ad1, Ad2, Ad4, Ad5, Ad7, and Ad21 .

## **4.3 Clinical experience with non-replicating Ad26 vectors expressing Env**

Non-replicating Ad26 vectors expressing the Env antigen have been tested in humans as part of three Phase 1 studies under the IPCAVD (Integrated Preclinical/Clinical AIDS Vaccine Development) NIH-sponsored program. In addition to providing safety data about non-replicating Ad26 vectors, these studies also provide supporting safety data about the use of Env inserts. These inserts are similar to the MOS1.HIV-Env insert (69% sequence overlap); MOS1.HIV-Env itself has not previously been tested in humans.

In IPCAVD001, a non-replicating Ad26 vector expressing EnvA.01 (Ad26.ENVA.01) was evaluated in a dose escalation study in 60 healthy, HIV-1 uninfected adults . Ad26.ENVA.01 vaccine was generally safe and well-tolerated at all doses tested ( $10^9$  through  $10^{11}$  vp, given intramuscularly) and up to 3 vaccinations. There were no vaccine-related SAEs. At the  $10^{11}$  dose, reactogenicity (fatigue, myalgias, and chills) was seen 12 hours after the 1st vaccination and resolved spontaneously. These symptoms were not seen after the 2nd vaccination. Consistent Env antibody titers and Env T cell responses were seen following the prime which increased after the 6 month boost and were durable at 1 year in vaccinated volunteers.

In a follow up study IPCAVD003, Ad26.ENVA.01 was tested in 24 healthy, HIV-1 uninfected adults to obtain a detailed evaluate of safety, mucosal immunogenicity, and innate immune responses following intramuscular immunization . The majority of volunteers reported mild or no tenderness at the vaccination site. Nine out of 18 vaccine recipients experienced at least 1 systemic reactogenicity symptom that was moderate or severe. In the 5 vaccine recipients who experienced at least 1 systemic severe reactogenicity symptom, these symptoms largely occurred between day 0 to 1 and were

typically a combination of headache, chills, joint pain, myalgia, and malaise/fatigue. There were no study product related SAEs. All volunteers developed detectable Ad26-specific Nabs, and 16 of 18 volunteers had detectable peripheral EnvA IgG ELISA titers. Mucosal EnvA-specific IgG ELISA responses were detected in 11 of 18 volunteers. EnvA-specific CD8+ and CD4+ T cell responses were also detected in the majority of volunteers. There were stable levels of Ki67+ cellular activation in total and vector specific CD4+ T lymphocytes following Ad26.ENVA.01 vaccination. There was no increase in CCR5 expression in total or vector specific CD4+ T lymphocytes in PBMCs or colorectal mucosa following vaccination.

Finally, in IPCAVD004, Ad26.ENVA.01 and Ad35Env vaccines were evaluated in various prime/boost combinations in 218 healthy HIV-1 uninfected adults in the US and in South and East Africa. The majority of both local and systemic reactogenicity reactions were graded as mild or moderate and resolved spontaneously. There were three unrelated SAEs. There was induction of Ad26 Nabs and EnvA ELISA titers in the majority of vaccinees, as well as detectable T cell responses.

## 5 OBJECTIVES

### Primary Objective

- To evaluate the safety and tolerability of a single oral administration of rcAd26.MOS1.HIV-Env HIV-1 vaccine administered in a dosage escalation of  $10^8$ ,  $10^9$ ,  $10^{10}$ , and  $10^{11}$  viral particles.

### Secondary Objectives

- To evaluate the shedding of rcAd26.MOS1.HIV-Env in rectal and oropharyngeal secretions.
- To evaluate humoral and cellular immune responses elicited by four increasing dosages of rcAd26.MOS1.HIV-Env HIV-1 vaccine.

### Exploratory Objectives

- To perform additional host response assays including measurement of Ad26-specific antibodies, HIV-1-specific antibody-dependent cell-mediated cytotoxicity (ADCC) and cell-mediated viral inhibition (ADCVI) assays, epitope mapping of T lymphocytes by ELISPOT, gene expression profiling, and analysis of mucosal humoral immune responses.
- To investigate the possibility of transmission of rcAd26.MOS1.HIV-Env to volunteers' household contacts after volunteers leave isolation unit.

## 6 STUDY DESIGN

This is a phase 1 trial of an oral, replication competent adenovirus 26-vectored HIV-1 vaccine. Because the vaccine is replication competent, volunteers will be housed in an isolation unit from day -2 through day 9 in order to limit any transmission of the viral vector if shedding occurs. The trial will be conducted under a placebo controlled, double-blind, randomized allocation of study product. This design is intended to reduce the likelihood of observer bias, provide control for confounding variables of intercurrent illness, and aid in the interpretation of laboratory data. The study will also be conducted using a dose-escalation design, wherein the group receiving the lowest dose (group 1) will be monitored for at least 9 days following vaccination before planned PSRT and SMC safety reviews prior to enrollment in the next group. Shedding data will not be available for inclusion in this safety review (see Section 6.2). There are four groups in the study and blinding will be maintained to vaccine or placebo within each group as noted in the table below.

**Table 1: Study Schema**

| Study Group* | rcAd26.MOS1.HIV-Env / Placebo | Dosage (Day 0)                                                                                                                                                                                                                                             | Delivery | Setting     |
|--------------|-------------------------------|------------------------------------------------------------------------------------------------------------------------------------------------------------------------------------------------------------------------------------------------------------|----------|-------------|
| 1            | 5 / 1                         | 10  vp / Placebo                                                                                                                                                                                                                               | PO       | Isolation** |
| 2            | 5 / 1                         | 10  vp / Placebo                                                                                                                                                                                                                               | PO       | Isolation   |
| 3            | 5 / 1                         | 10  vp / Placebo                                                                                                                                                                                                                              | PO       | Isolation   |
| 4            | 5 / 1                         | 10  vp / Placebo                                                                                                                                                                                                                              | PO       | Isolation   |
| Total Number | 20 / 4                        | 
*Starting with Group 1, each group will be sequentially enrolled following PSRT and SMC reviews of safety data for a period of at least 9 days post vaccination.
 
**Volunteers will be housed in an isolation unit from day -2 through day 9.
 |          |             |

It is anticipated that enrollment will be completed within a 6-month period, and that volunteers will be actively followed for 12 months.

### 6.1 Safety Assessment

On Days 0-9 post vaccination of the isolation portion of the study, a study clinician (MD, NP, and/or nurse) will assess the volunteers with a directed medical history and abbreviated physical examination (once daily, noting any medication use), review the volunteer's reactogenicity diary card (once daily), and check vital signs (twice daily). Any unsolicited adverse events observed or reported at any time of day will also be noted.

After the completion of the isolation portion of the study, adverse events will be assessed at follow up visits, as detailed in the Schedule of Procedures (Section 18.5). Hematology and blood chemistries will also be assessed as detailed in the Schedule of Procedures.

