## **9.2 Clinical and Laboratory Evaluations – Volunteers**

Please see Sections 18.5 and 18.7 for a concise outline of study procedures. Screening should occur within 56 days of enrollment. Volunteers will be admitted to the isolation facility 2 days before the vaccine is administered in order to allow for any incubating illness to emerge prior to the administration of the vaccine. During the isolation period, volunteers will be seen twice daily. For visit windows, refer to the Schedule of Procedures (Section 18.5).

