### **12.2 Endpoints**

Safety and tolerability:

- Any adverse events within 4 months following vaccination (SAEs within 12 months following vaccination)
- Moderate or greater unsolicited adverse events related to study product (i.e., suspected adverse reactions) within 4 weeks post-vaccination
- Moderate or greater solicited reactions within 9 days post-vaccination

Shedding:

- Proportion (95% CI) of volunteers per dose group with positive responses and mean response per group with 95% CI.
  - Rectal/oral shedding: real-time PCR for rcAd26.MOS1.HIV-Env at 1, 2, 3, 4, 5, 6, 7, 8, 9, 12, 17, 21, 7, 12, 21, and 28 days after vaccination.

Immunogenicity:

- Proportion (95% CI) of volunteers per dose group with positive responses and mean response (e.g. GMT) per group with 95% CI.
  - Cellular immunogenicity: Env-specific ELISPOT responses at 4 weeks after vaccination.
  - Humoral immunogenicity: Env-specific binding antibody titers at 4 weeks after vaccination.

- Durability of responses: immunogenicity assays at 4, 8 and 12 months after vaccination.

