| Informed Consent                                | X       |                  |    |     |     |     |     |     |     |     |     |     |     |    |    |    |     |                     |          |          |              |  |
| Assessment of Understanding                     | X       |                  |    |     |     |     |     |     |     |     |     |     |     |    |    |    |     |                     |          |          |              |  |
| HIV Risk Assessment                             | X       |                  |    |     |     |     |     |     |     |     |     |     |     |    |    |    |     |                     |          |          | X            |  |
| HIV Risk Reduction Counseling                   | X       |                  |    | X   |     |     |     |     |     |     |     |     |     | X  | X  | X  | X   | X                   | X        | X        | X            |  |
| HIV Test Counseling                             | X       |                  |    |     |     |     |     |     |     |     |     |     |     |    |    |    | X   |                     |          |          | X            |  |
| Pregnancy Prevention Counseling                 | X       |                  |    | X   |     |     |     |     |     |     |     |     |     | X  | X  | X  | X   |                     |          |          |              |  |
| Comprehensive Medical History                   | X       |                  |    |     |     |     |     |     |     |     |     |     |     |    |    |    |     |                     |          |          |              |  |
| Intercurrent Illness                            |         | X                | X  | X   |     |     |     |     |     |     |     |     |     | X  | X  | X  | X   | X                   |          |          |              |  |
| Concomitant Medications/Supplements             | X       | X                | X  | X   | X   | X   | X   | X   | X   | X   | X   | X   | X   | X  | X  | X  | X   | X                   |          |          |              |  |
| Complete Physical Exam                          | X       |                  |    |     |     |     |     |     |     |     |     |     |     |    |    |    |     |                     |          |          | X            |  |

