| Abbreviated Physical Exam (see SOM)             |         | X                |    | X   | X   | X   | X   | X   | X   | X   | X   | X   | X   | X  | X  | X  | X   | X                   | X        |          |              |  |
| Weight                                          | X       |                  |    |     |     |     |     |     |     |     |     |     | X   |    |    |    |     |                     |          |          | X            |  |
| Height                                          | X       |                  |    |     |     |     |     |     |     |     |     |     |     |    |    |    |     |                     |          |          |              |  |
| Vital Signs                                     | X       | X                |    | BID | BID | BID | BID | BID | BID | BID | BID | BID | BID | X  | X  | X  | X   | X                   | X        | X        |              |  |
| Reactogenicity Assessment                       |         |                  |    | X   | X   | X   | X   | X   | X   | X   | X   | X   | X   |    |    |    |     |                     |          |          |              |  |
| Adverse Event Evaluation                        |         |                  |    | X   | X   | X   | X   | X   | X   | X   | X   | X   | X   | X  | X  | X  | X   | X                   | SAE Only | SAE Only |              |  |
| Social Impact Assessment                        |         |                  |    |     |     |     |     |     |     |     |     |     |     |    |    |    |     |                     |          |          | X            |  |
| Unblinding                                      |         |                  |    |     |     |     |     |     |     |     |     |     |     |    |    |    |     |                     |          |          | X            |  |
| LABORATORY TESTS                                |         |                  |    |     |     |     |     |     |     |     |     |     |     |    |    |    |     |                     |          |          |              |  |
| Syphilis, HBV, HCV                              | X       |                  |    |     |     |     |     |     |     |     |     |     |     |    |    |    |     |                     |          |          |              |  |

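### No graded pre-dose baseline is scheduled for the solicited symptoms, although volunteers are inpatients from Day -2, so a complaint already present at dosing can count as a solicited reaction

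*Protocol*

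**What the plan says.** Section 6 states that "volunteers will be housed in an isolation unit from day -2 through day 9". Section 9.2 gives the reason for the early admission: "Volunteers will be admitted to the isolation facility 2 days before the vaccine is administered in order to allow for any incubating illness to emerge" before dosing.

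Section 6.1 sets the daily assessments: "On Days 0-9 post vaccination of the isolation portion of the study, a study clinician (MD, NP, and/or nurse) will assess the volunteers". These include the instruction to "review the volunteer's reactogenicity diary card (once daily"). In the schedule in 18.5, the row "Reactogenicity Assessment" is marked on Days 0 to 9 and blank on Days -2 and -1.

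Section 12.2 defines the endpoint as "Moderate or greater solicited reactions within 9 days post-vaccination". It carries no reference to baseline and no relatedness condition. The unsolicited endpoint beside it does require relatedness to study product.

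The reactions named in 10.1.2.3 are fever, fatigue/malaise, headache, myalgia, arthralgia, chills, nausea and vomiting.

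Some pre-dose observation is planned. In 18.5, "Intercurrent Illness" and concomitant medications are marked on Days -2, -1 and 0, "Abbreviated Physical Exam (see SOM") on Days -2 and 0, and vital signs once on Day -2 and twice on Day 0. Section 10.1.2.2 collects AEs from signature of the consent form and sends signs or symptoms present before study start to Medical History.

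**The concern.** Apart from fever, the named reactions are non-specific symptoms that healthy people report without any vaccine. When such a symptom is solicited after an exposure, the usual way to interpret it is to know whether the same person had it, and at what grade, just before. This protocol brings volunteers in two days early but schedules no use of the diary card on those days.

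Tolerability is part of the primary objective, and under 10.9 the SMC reviews Day 0 to Day 9 data before each escalation. A background complaint in one of five vaccinees makes up a fifth of that group's result. Each group has a single placebo recipient to set it against. A later analysis plan can say how symptoms present at dosing are to be counted, but it cannot recover graded pre-dose symptoms that were never collected.

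**Working it through.** **1. Pre-dose coverage, from 6.1, 18.5 and 10.1.2.2**

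| Item | Day -2 | Day -1 | Day 0 |
|---|---|---|---|
| Reactogenicity Assessment | blank | blank | marked, before or after dose not stated |
| Adverse Event Evaluation | blank | blank | marked |
| Intercurrent Illness | marked | marked | marked |
| Concomitant medications | marked | marked | marked |
| Abbreviated examination | marked | blank | marked |
| Vital signs | once | blank | twice daily |

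No row schedules grading of the solicited symptoms before the dose. On Day -1 the only marked items in this list are the illness check and medications. The Adverse Event Evaluation row begins on Day 0, whereas 10.1.2.2 collects AEs from consent, so the text and the schedule disagree for the two days in question.

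**2. The protocol's own precision figure**

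Section 12.3 gives upper 95% Clopper-Pearson limits for zero events of 60.2% (n = 4) and 52.2% (n = 5). The two-sided limit is 1 − 0.025^(1/n).

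- n = 4: 1 − 0.025^(1/4) = 60.2%.
- n = 5: 1 − 0.025^(1/5) = 52.2%.

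Both reproduce. For the single placebo recipient in a group, n = 1: 1 − 0.025 = 97.5%. Zero events in one person says almost nothing about the background rate. Pooling all four improves this only to 60.2%, and by 6.6 it mixes one-capsule with ten-capsule regimens.

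**3. How often background alone could appear**

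The documents give no background rate. Assume that a proportion p of volunteers would have at least one moderate or greater listed symptom over Days 0 to 9 for reasons other than vaccine, with p between 10% and 20%.

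| Event | Formula | p = 10% | p = 20% |
|---|---|---|---|
| At least 1 of 5 vaccinees | 1 − (1 − p)^5 | 41.0% | 67.2% |
| The same, and that group's placebo recipient shows none | [1 − (1 − p)^5](1 − p) | 36.9% | 53.8% |
| At least 1 of 4 pooled placebo recipients | 1 − (1 − p)^4 | 34.4% | 59.0% |

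**4. What a pre-dose diary could identify**

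Let s be the share of affected volunteers whose complaint is already present before the dose. The chance that at least one of five vaccinees has such a complaint is 1 − (1 − sp)^5. This is 0 at s = 0 and reaches 41.0% or 67.2% only at s = 1. The documents do not give s, so the identifiable part lies somewhere between these ends.

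**The case against.** The protocol nowhere says that pre-existing complaints count as reactions. It checks for intercurrent illness on three days, examines volunteers on Days -2 and 0, and collects AEs from consent. AEs are graded on the DAIDS table, which has rows for the same symptoms, so a pre-dose headache recorded as an AE would carry a grade. Section 10.1.2.4 also has clinicians looking for AEs twice daily during isolation, which could be read to include the pre-dose days. This stands as far as it goes: baseline complaints are not invisible. What is missing is active daily solicitation on the same card. The schedule does not prompt AE evaluation before Day 0, and it is unclear whether a symptom that begins in the unit on Day -1 belongs in Medical History.

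A reader might infer that 41% to 67% is the error caused by the missing baseline. The documents do not support that. It is total background at an assumed rate. Section 6.2 bars volunteers from leaving their rooms after immunization, so symptoms that this confinement first provokes would still appear as new, and only concurrent placebo can address them.

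A reader might also infer that the endpoint should be replaced by new-or-worsened reactions. That is a debatable exchange in a first-in-human trial: a genuine Grade 2 headache after the dose would be dropped if a resolved Grade 2 headache had been noted on Day -2. Counting every solicited reaction whatever its cause is a defensible cautious choice.

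Finally, Table 2, footnote 3, removes all the listed symptoms except fever from the Grade 3 or 4 related-AE pausing rule, and fever has an objective pre-dose reading. The effect on automatic pauses is therefore small.

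**Conclusion.** The point holds as a gap in data collection. Two inpatient pre-dose days are available, no graded baseline is scheduled for the solicited symptoms, the timing of the Day 0 entry is not fixed, and the endpoint wording lets a complaint present at dosing be counted. The existing checks fill the gap only in part, and the text and schedule disagree on when AE collection starts.

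Placebo cannot make up for this: the upper limit after zero events is 97.5% for one recipient and 60.2% for four. The 41% to 67% rests on an assumed rate of 10% to 20% and independence between volunteers. It shows how readily background could appear in a group of five, not how much the fix would remove.

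The consequence is for interpretation of tolerability and for the SMC's review before each escalation. It warrants a change because the change is cheap and the data cannot be collected later.

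**What to change.** - In 6.1 and the Reactogenicity Assessment row of 18.5, add the same diary card on Day -2, Day -1 and Day 0 before dosing, and label the existing Day 0 entry as post-dose.
- In 12.2, keep the count of all moderate or greater solicited reactions as the main endpoint. Add a supplementary tabulation of those that are new or worse in grade than before the dose.
- Reconcile 10.1.2.2 with the Adverse Event Evaluation row of 18.5 on when AE collection begins.

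The cost is three short entries per volunteer (3 × 24 = 72 for the trial, plus those of any back-up volunteers admitted under 9.8.4) and one extra table. No visit or blood draw is added. The diary will not separate symptoms that first arise after dosing, and the report should say so.
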